# Effectiveness of telerehabilitation programme following surgery in shoulder impingement syndrome (SIS): study protocol for a randomized controlled non-inferiority trial

**DOI:** 10.1186/s13063-017-1822-x

**Published:** 2017-02-23

**Keywords:** Telerehabilitation, SIS (shoulder impingement syndrome) physiotherapy, Surgery procedure, Telemedicine

## Abstract

**Background:**

Shoulder pain is common in society, with high prevalence in the general population. Shoulder impingement syndrome (SIS) is the most frequent cause. Patients suffer pain, muscle weakness and loss of movement in the affected joint. Initial treatment is predominantly conservative. The surgical option has high success rates and is often used when conservative strategy fails. Traditional physiotherapy and post-operative exercises are needed for the recovery of joint range, muscle strength, stability and functionality. Telerehabilitation programmes have shown positive results in some orthopaedic conditions after surgery. Customized telerehabilitation intervention programmes should be developed to recover shoulder function after SIS surgery. The objective of this study is to evaluate the feasibility and effectiveness of a telerehabilitation intervention compared with usual care in patients after subacromial decompression surgery.

**Methods:**

We will compare an intervention group receiving videoconferences and a telerehabilitation programme to a control group receiving traditional physiotherapy intervention in a single-blind, randomized controlled non-inferiority trial study design.

**Discussion:**

Through this study, we will further develop our preliminary data set and practical experience with the telerehabilitation programmes to evaluate their effectiveness and compare this with traditional intervention. We will also explore patient satisfaction and cost-effectiveness. Patient enrolment is ongoing.

**Trial registration:**

ClinicalTrials.gov, NCT02909920. 14 September 2016.

**Electronic supplementary material:**

The online version of this article (doi:10.1186/s13063-017-1822-x) contains supplementary material, which is available to authorized users.

## Background

Shoulder pain is common in society, with 7–27% of the adult population experiencing shoulder pain at any one time, and 7–67% of people experiencing shoulder pain in their lifetime [1]. Shoulder pain is highly prevalent within the general population, along with back and neck pain. Studies suggest that shoulder impingement syndrome (SIS) is the most common cause of shoulder pain [2]; it is estimated that SIS accounts for 44–60% of medical visits for shoulder pain [3, 4].

A prevalence of 78 cases per 1000 inhabitants has been reported for SIS, and review studies relate variations in prevalence between 70 and 200 per 1000 adults, leading to a significant consumption of healthcare resources and productive losses due to employee absenteeism [5]. Approximately 20% of expenditures for disablement by musculoskeletal disorder are consigned to subjects with shoulder disorders [6].

A socio-economic study with 6 months’ follow-up in patients with shoulder pain estimated an average cost of 326 euros per subject in healthcare, and the total cost was 2069 euros taking into account the average economic loss associated with absenteeism [6].

SIS has been defined as the compression and mechanical abrasion of the rotator cuff structures as they pass beneath the coracoacromial arch during elevation of the arm [7]. Repetitive activity at or above the shoulder during work or sports represents the main risk factor for SIS. As with many shoulder disorders, increasing age also predisposes one to SIS [8]. Patients with SIS suffer from pain, weakness and loss of movement of the affected shoulder. Causes of impingement include acromioclavicular joint arthritis, calcified coracoacromial ligament, structural abnormalities of the acromion and weakness of the rotator cuff muscles [9].

This musculoskeletal disorder affects the structures of the subacromial space, which are the tendons of the rotator cuff and the subacromial bursa. Subacromial impingement syndrome appears to result from a variety of factors. Evidences exist to support the presence of the following anatomical factors: inflammation of the tendons and bursa, degeneration of the tendons, weak or dysfunctional rotator cuff musculature, weak or dysfunctional scapular musculature, posterior glenohumeral capsule tightness, postural dysfunctions of the spinal column and scapula and bony or soft tissue abnormalities of the borders of the subacromial outlet. These entities may lead to or cause dysfunctional glenohumeral and scapulothoracic movement patterns. These various mechanisms, singularly or in combination, may cause subacromial impingement syndrome [10]. However, recent literature suggests that SIS is, in fact, the final result of many shoulder diseases and can be regarded as a descriptive term for a broad spectrum of symptoms rather than a single diagnosis [11].

Initial treatment of SIS is predominantly conservative, including rest, non-steroidal anti-inflammatory drugs, corticosteroid injections, physical therapy and various forms of exercise and manual therapy. When symptoms persist for periods longer than 3 months, it is common to refer the case for a re-evaluation by an orthopaedic surgeon [12].

Surgical and non-surgical strategies are used to treat SIS. An article on the effectiveness of post-surgical interventions for SIS has already been published [13], and high success rates have been noted as a result of surgical procedures [14, 15]. The most common surgical intervention for impingement is subacromial arthroscopic decompression (SAD). A Cochrane review comparing SAD with an open surgery approach concluded that neither procedure has been shown to be superior to the other [16].

Post-operative exercise therapy is also recommended, although its effectiveness is less documented. Early progressive exercises (range of motion and strengthening exercises) have been shown to result in greater improvements in range of motion at 3 and 12 months than later dynamic and strengthening exercises. Reductions in pain were similar for both regimens [17].

There is scarce evidence regarding the effectiveness of exercise programmes after decompression surgery for subacromial impingement syndrome. Also, there is currently no consensus about the most appropriate post-operative exercise strategy. With this argument, a recent multi-centre randomized controlled trial in Denmark has concluded that a standardized physiotherapy exercise intervention resulted in statistically significant and clinically relevant improvement in shoulder pain and function at 12 months when compared to usual care [18].

In addition to traditional physiotherapy, telerehabilitation programmes have demonstrated their effectiveness, validity and non-inferiority and presented significant advantages in neurological, cognitive and musculoskeletal diseases, providing an opportunity to define new social policies and intervention.

Telerehabilitation is a term used to describe the provision of rehabilitation services at a distance using telecommunications technology as the service delivery medium [19]. It has also been defined as the remote delivery of rehabilitative services, such as monitoring, training and long-term care, using telecommunications technology [20]. Therapists are using the technology in a variety of ways. Some of these include therapeutic interventions, remote monitoring of progress, education and training delivered to families, access to rehabilitation professionals, coordinating care with other professionals and providing networking for individuals with disabilities [21].

In the last 15 years, telerehabilitation within the larger realm of telehealth has been used to aid rural communities, with an emphasis on older adults, to improve and access healthcare services with the objective of decreasing cost and transportation issues [22]. As this technique continues to grow in popularity, the number of clients benefiting has increased, and telerehabilitation is now recognized as a bridge between the medical professional and the client [23].

Telerehabilitation for musculoskeletal disorders has been studied, and interesting conclusions have been published: ‘Adding an Internet-based protocol is more effective than education and exercise alone for persistent hip pain’ [24]; ‘Standard musculoskeletal assessment of lumbar pain is valid via telerehabilitation’ [25]; ‘Interactive virtual telerehabilitation program is at least as effective as conventional therapy after total knee arthroplasty’ [26]; ‘Noninferiority of in-home telerehabilitation is an effective alternative to face-to-face service of patients following a total knee arthroplasty’ [27]; ‘In-home teletreatment seems to be a promising way to dispense rehabilitation services for proximal humerus fractures’ [28]; and last, ‘statistically significant improvements in exercise self-efficacy, mobility, quality of life, and patient satisfaction after 30-day hip fracture telerehabilitation’ [29].

Therefore, studies with telerehabilitation interventions should continue and improve methodologically, addressing new diseases and becoming oriented to results that can be validated, standardized and integrated into healthcare policies.

## Methods

The aim of this study is to evaluate the feasibility and effectiveness of a customizable telerehabilitation intervention compared with usual care in patients after subacromial decompression surgery. Secondary objectives are to identify satisfaction and perception of patients regarding telerehabilitation intervention and to evaluate the cost-effectiveness of the intervention. Our hypothesis is that the clinical outcomes of the telerehabilitation intervention after shoulder surgery for SIS will be effective and not inferior to traditional therapy.

This is a single-blind, prospective, randomized clinical trial in the Rehabilitation service in Marbella’s Hospital Costa del Sol in Spain. This research project uses the guidelines on Standards for Quality Improvement Reporting Excellence (SQUIRE) [30]. A Standard Protocol Items Recommendations for Interventional Trials (SPIRIT) checklist is provided as Additional file 1, and the flow diagram for the study protocols is included as Fig. 1.

**Fig. 1 Fig1:**
[figure not shown]
Study design

### Patients

The study includes adults between 18 and 65 years of age, diagnosed with subacromial syndrome (shoulder impingement syndrome, SIS) according to the 10th Revision of the International Classification of Diseases ICD-9 CM 726.10, 726.12, and 726.19 [31].

Subjects will have received a surgical procedure arthroscopically (subacromial decompression with partial acromioplasty, with or without coracoacromial release) or surgical codes related to SIS [14]. Furthermore, patients must live in Spain during the intervention phase, should have computer equipment with an Internet connection (including one of the following devices: personal computer, notebook, tablet or smartphone) that they can access frequently and they should have an existing email account. Exclusion criteria will be as follows: patients who have had surgery on the shoulder before the first contact with this research; those whose interventions are not based on surgical codes recommended for SIS; and subjects who do not have full cognitive abilities to allow the use of new technology tools. Table 1 lists the inclusion and exclusion criteria in detail.

**Table 1 Tab1:** Inclusion and exclusion criteria

Inclusion criteria	Exclusion criteria
Adult between 18 and 65 years	Patients who received surgery in same shoulder before this research.
Subacromial syndrome diagnosis CIE-9 MC 726.10, 726.12, 726.19 issued by specialist in orthopaedic surgery or rehabilitation	Patients receiving surgical procedure non-based on the recommendations for subacromial syndrome
Receives surgical procedure (arthroscopy or open approach (subacromial decompression with partial acromioplasty, with or without coracoacromial release)) and prescription to start rehabilitation process.	Unfit cognitive ability to use technological tools
Lives in Spain during the investigation period	
Provides home computer with Internet technology (personal computer, laptop, tablet or smartphone)	
Skills and knowledge to access email	

The strategies for achieving adequate participant enrolment to reach target sample size include multidisciplinary collaboration of the Hospital Costa del Sol Team (Orthopaedic Surgeon, Head of Rehabilitation and physiotherapist’s team). The employees have been informed about the characteristics of the study via personal interviews and a project presentation.

### Randomization and single blinding

Before patient inclusion, a research secretary will generate the allocation sequence and randomly assign patients consecutively with opaque sealed numbered envelopes. We will use a computerized random number generator. The research secretary will be instructed not to reveal the allocation sequence to any of the research team. The nature of the intervention in both groups does not allow blinding of patients and physiotherapists. It is therefore a single-blind study, where the evaluator does not know the nature of the intervention.

### Intervention

Patients will be randomly assigned to (1) the Telerehabilitation (TR) group or (2) the Traditional Physiotherapy (PT) group. After randomization, patients in both groups will receive an initial evaluation. Data will be collected by a blinded evaluator and will be integrated into our research databases. The assessor and the patients will be instructed not to reveal the type of intervention they are using. The TR group will receive a customized exercises programme through a web application that allows the physiotherapist to generate videos, images and parameters of each exercise programme and send them via email.

The telerehabilitation programme describes the exercises to be performed, the number of repetitions (depending on the level of training) and criteria for progression. Patients will be initially supervised by a physiotherapist, who will conduct three individual videoconference training sessions (30 minutes each session) to ensure proper execution of exercises and encourage patient adherence.

Patients will be instructed to follow a 12-week (5 days/week) self-workout video exercise regimen following the guidelines of the telerehabilitation programme as well as a supporting document called the Telerehabilitation Patient Manual (this document is held by the corresponding author).

At baseline patients will receive advice on general care in physical activity, and issues concerning the intake of analgesics will be based on general practice and specialist advice. Patients will be warned not to practise any specific training for the shoulder during the intervention period (training not recommended by the physiotherapist). The physiotherapist will record any deviations from adherence and practice, noting any adverse impact on the exercises.

The PT group will receive assistance in the Costa del Sol Hospital’s physiotherapy department consisting of one-to-one physical therapy (manual therapy, home exercise programmes and other physiotherapy techniques) in a 12-week programme (5 days/week).

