### Outcome measures

The initial assessment includes clinical interview and the following shoulder tests: the Constant–Murley Test (CM) (see Additional file 2) and the Simple Shoulder Test (SST) (see Additional file 3).

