#### Primary outcome measures

At 4, 8 and 12 weeks, we will use the CM. The CM is an assessment tool universally used and accepted for shoulder function [32]. We will assess changes in the CM scores from baseline. The CM has a 100-point scoring system that is divided into four domains: pain (maximal 15 points), daily life activities (maximal 20 points), painless range of motion (maximal 40 points) and abduction strength evaluation (maximal 25 points) according to the methods described by Constant [33].

In addition we will use the SST Spanish validated version, an instrument that features 12 one-dimensional Yes/No answer questions [34]. The SST is a short questionnaire (2–3 minutes) — easy to understand and complete — and has validity and comparability with other subjective questionnaires [35]. The total score of 12 questions (2 related to pain, 7 on the force and 3 on the range of motion) [35], where 0 is the worst result and 100 is the best shoulder function measured, is calculated based on the number of positive responses multiplied by 100 [35]. The internal consistency of the test was measured by Cronbach’s alpha = 0.85 [36].

The impact of shoulder disorders can be evaluated from different perspectives. Traditionally, evaluation has been made at the local level, focusing on the functional aspects of the pathology and evaluating the range of motion, strength or pain [37]. Currently, there is an increasing trend towards the use of outcome measures that are subjectively reported by patients, assessing the perception of their own functional status [38]. These questionnaires are becoming widely used tools in the evaluation of treatment both in clinical practice and in medical research [34]. It is critical to employ valid and reliable research measures, and they must also be culturally and linguistically appropriate [39]. Current evidence supports the use of the SST questionnaire for longitudinal studies and clinical trials [34]. The SST is among the three subjective questionnaires that score higher reliability, responsiveness to change and interpretation [34]. In addition, the SST has been translated and cross-culturally adapted into Spanish with adequate psychometric properties [40].

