### Data collection and sources of data

Once patients are informed and randomly assigned to one group, we will be able to collect data for statistical analysis. This data collection will take place in the period from October 2016 to March 2017. An independent evaluator in the rehabilitation services will conduct initial assessment and the different measures at 4, 8 and 12 weeks. The data will be added to the database created for that purpose and administered by the principal investigator for statistical analysis.

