### Statistical analysis

The trial results will be presented as a summary of the outcomes in each group, along with the estimated effect size and its precision. The statistical analysis will be performed in accordance with both an intent-to-treat analysis and a per-protocol analysis to have the maximum information about the treatment outcomes.

Frequency tables and histograms will present affiliation data for the participants. We will carry out a descriptive statistical analysis of the different variables, using frequency tables, bar charts and sector charts with the aim of having as much information as possible for exploration and analysis.

The study’s central hypothesis will be tested by comparing change in the CM score between the two groups for the intervention shoulder Appendix 1. To compare independent variables between the two groups, the Student’s *t* test will be used if validity criteria are met; otherwise, we will use the non-parametric approach Appendix 2. As other studies have shown [45], significant departures of normality are not expected. The difference in the evolution of the CM score between treatment groups from baseline to 4, 8 and 12 weeks follow-up will be tested using repeated measurements analysis of variance.

A non-inferiority study seeks to determine whether a new intervention is therapeutically equivalent, or not less equivalent, to an existing intervention reference [46]. In this study, the new intervention TR will be compared with the conventional standard of rehabilitation after SIS in Spain.

Studies have presented results on the minimal clinically important differences for shoulder outcome measures (Fig. 2) [47, 48]. Recently, a study showed minimal detectable change ≥10 points in the CM score and a standard deviation (SD, 11.2) for patients with SIS [45]. Therefore, the non-inferiority criteria will be evaluated comparing the differences between groups with a non-inferiority margin of 10 points in the CM score, which is considered to be a clinically relevant change [49, 50].

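### The initial CM and SST are placed after randomization in an open-label trial, so knowledge of the arm can shift the baseline from which the primary change score is taken

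*Protocol article*

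**What the plan says.** All references are to the protocol article, Methods.

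- **Order of steps.** The Intervention section says: "After randomization, patients in both groups will receive an initial evaluation". The section on data collection gives the same order: "Once patients are informed and randomly assigned to one group, we will be able to collect data for statistical analysis".
- **Content of the initial evaluation.** Outcome measures: "The initial assessment includes clinical interview and the following shoulder tests: the Constant–Murley Test (CM"), followed by the SST.
- **Blinding.** Randomization and single blinding: "The nature of the intervention in both groups does not allow blinding of patients and physiotherapists". The evaluator is blinded; the Intervention section says "Data will be collected by a blinded evaluator and will be integrated into our research databases", and adds "The assessor and the patients will be instructed not to reveal the type of intervention they are using".
- **Use of baseline.** Primary outcome measures: "We will assess changes in the CM scores from baseline". In Statistical analysis, the "central hypothesis will be tested by comparing change in the CM score between the two groups".

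The article shows no CM or SST taken before allocation, and no step that keeps the arm from the patient until baseline is complete.

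**The concern.** A baseline taken before allocation cannot depend on the arm. One taken afterwards can, if the patient knows the arm and the instrument records what the patient says. A patient who is disappointed or reassured by the allocation may rate pain and daily function differently before any treatment has begun.

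The SST consists of the patient's own yes/no answers. In the CM, pain carries 15 points and daily activities 20, so 35 of 100 points are patient-reported. Pain-free range of motion (40) and strength (25) also depend partly on reported pain or effort.

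What is at stake is the primary comparison. A lower reported baseline in TR makes its gain look larger and favours non-inferiority. A shift the other way makes a true non-inferiority harder to show. Follow-up reporting is unavoidably open in this trial, whereas the baseline could be protected.

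**Working it through.** **1. Does the text fix the order?** Yes. Two sections, Intervention and Data collection, put assessment after assignment, so it is not a single loose phrase. Outcome measures puts both tests in that assessment.

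**2. Do patients know their arm at that moment?** This is inferred. Allocation is open, baseline follows assignment, and patients are told not to disclose their intervention, which presupposes that they know it at some point. Nothing shown delays that knowledge until after baseline.

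**3. How a shift enters the estimate.** Let s0 be the arm difference (TR minus traditional physiotherapy, PT) in reporting at baseline caused by knowing the arm, and s1 the same at follow-up.

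Bias in the difference in change = s1 − s0.

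If the effect is gone by follow-up (s1 = 0), a baseline shift of −b in TR adds +b to its apparent gain. If it persists fully (s1 = s0), it cancels. The figures below are for s1 = 0.

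**4. Inputs.** From Statistical analysis and the sample size paragraph after Fig. 2: margin 10, SD of CM improvement 11.2, power 90%, significance level 5% (sidedness not stated), 22 per group. Assumed: one-sided 5%, and b = 1, 2 or 3 points. The documents give no value for b.

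**5. The plan's own figure.** n per group = 2 × [11.2 × (1.645 + 1.282) / 10]² = 21.5, so 22. The stated size is reproduced with a one-sided 5% level. A one-sided 2.5% level would give 26.4, so 27. This supports one-sided 5% as the working assumption.

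**6. Effect of a shift.** SE = 11.2 × √(2/22) = 3.377. With 42 degrees of freedom the one-sided 5% critical value is 1.682. With a noncentral t distribution T(δ) of noncentrality δ:

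- False non-inferiority at a true difference of −10, shift favouring TR: P[T(b/SE) > 1.682].
- Power at a true difference of 0, shift against TR: P[T((10 − b)/SE) > 1.682].

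| Assumed shift b (points) | False non-inferiority, shift favours TR | Power, shift against TR |
|---|---|---|
| 0 | 5.0% | 89.8% |
| 1 | 8.8% | 83.6% |
| 2 | 14.4% | 75.4% |
| 3 | 22.0% | 65.3% |

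**7. Sensitivity.** A half-point shift gives a false-claim rate of 6.7%. With 15% dropout (44 × 0.85 ≈ 37 patients, 19 + 18) the false-claim rates for 1, 2 and 3 points are 8.4%, 13.3% and 19.9%. At one-sided 2.5% with 22 per group, the rate rises from 2.5% to 4.7%, 8.4% and 13.8%.

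**The case against.** The strongest case against the point has four parts.

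- **Knowledge of the arm at baseline is not documented.** The article does not say when the patient is told. The obstacle to blinding is the nature of the treatments, which have not started at baseline, and the instruction not to disclose fits follow-up visits at least as well. In the data collection sentence, being informed may mean being informed about the study. The study design figure and the SPIRIT checklist are not shown and may give the order. This stands: the text supports saying that patients probably know, and no more.
- **A blinded evaluator collects the data.** This is a real safeguard for the evaluator's scoring and must be credited. It does not reach what an unblinded patient reports.
- **The size is assumed.** The shift, its direction and the one-sided level are not in the documents, and a shift against TR makes a false claim less likely. This stands, and is why both directions are shown.
- **A persistent shift cancels.** Patients are equally unblinded at 4, 8 and 12 weeks. This stands as a limit on the mechanism. It also means that reordering cannot secure the nominal error rate: with a clean baseline the bias is s1, the follow-up part.

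A reader might also infer that the order undermines the intention-to-treat analysis, because a patient who withdraws on learning the arm has no baseline. The documents do not support this as a separate fault: such a patient would usually have no follow-up CM either, so an earlier baseline would not produce an observed change. A reader might further infer that baseline is spoiled as an adjustment covariate, but Statistical analysis names a t test on change and a repeated-measures analysis of variance, with no baseline covariate.

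**Conclusion.** The point holds as a should-fix. As written, the baseline of the primary change score is taken after allocation in a trial that cannot blind patients, and nothing shown protects its patient-reported content from knowledge of the arm. The resulting bias is possible, not demonstrated.

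The conclusion rests on two conditions: that patients know their arm at the initial evaluation, which is probable but unstated, and that some of the reporting effect has gone by follow-up. Under those conditions, shifts that are small beside the 10-point margin matter. At 2 points, the false-claim risk goes from 5% to about 14% in one direction, and power from about 90% to about 75% in the other.

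A reader might infer that the trial is biased towards non-inferiority. The documents do not support that, because they fix neither the direction nor the size of any shift.

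**What to change.** - Have the blinded evaluator complete the CM and SST after consent and before the envelope is opened, or at least before the patient learns the arm. State this order in both Intervention and Data collection.
- If this is already the practice, correct the wording of those two sections.
- For patients already enrolled, record whether baseline preceded knowledge of the allocation, report the numbers by arm, and add a descriptive sensitivity analysis. With 44 patients it can show little more than whether the two subsets look alike.

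**Cost.** No extra patients, staff or procedures, and the sample size stays at 22 per group. Visit logistics change slightly; the article does not say whether randomization and the initial evaluation share a visit. Because enrolment is ongoing, a change now leaves both orders mixed within a sample of 44. Bias in follow-up reporting from open allocation remains and should be acknowledged as a limitation.

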Possible adverse events to be considered are a lack of improvement and positive developments in the range of movement, in terms of pain, muscle strength and function of the operated limb. Performing movements with excess load that cause tendon inflammation and muscle strain should also be considered as adverse events. Patients will be informed about the importance of warning the healthcare professional of any incident or misadventure in their recovery and their right to give up their participation at any time during the research.

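### Harms are noted through contacts that differ by up to 20:1 between arms, so a harms comparison is open to differential ascertainment; separately, lack of improvement is listed as an adverse event

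*Protocol article*

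**What the plan says.** Two routes for noting harm are stated.

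- **Physiotherapist's notes** (Protocol article, Intervention): "The physiotherapist will record any deviations from adherence and practice, noting any adverse impact on the exercises". The sentence follows the description of the TR regimen and precedes the paragraph on PT. It does not name an arm. Randomization and single blinding says that physiotherapists and patients cannot be blinded.
- **Patient's initiative** (Protocol article, Discussion): "Patients will be informed about the importance of warning the healthcare professional of any incident or misadventure in their recovery".

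Scheduled contact differs by arm (Intervention). A physiotherapist supervises TR patients at the start, "who will conduct three individual videoconference training sessions (30 minutes each session"), and after that "Patients will be instructed to follow a 12-week (5 days/week) self-workout video exercise regimen". The PT arm attends the hospital department for "one-to-one physical therapy (manual therapy, home exercise programmes and other physiotherapy techniques) in a 12-week programme (5 days/week").

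Data collection and sources of data has an independent evaluator seeing both arms at baseline and at 4, 8 and 12 weeks for the outcome measures. No harm question is described there.

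On what counts as harm, the Discussion says: "Possible adverse events to be considered are a lack of improvement and positive developments in the range of movement", and continues with pain, strength and function of the operated limb. A separate sentence adds tendon inflammation and muscle strain caused by overload.

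**The concern.** There are two separate problems.

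**Ascertainment.** Both stated routes depend on contact with a professional or on the patient's initiative. Scheduled physiotherapist contact is far lower in the arm that exercises mostly alone, and overload injury is a harm the article itself names. If a short-lived strain is less likely to be noted in TR, TR can appear as safe as PT, or safer, because it was watched less. A trial meant to inform care policy should not leave that possibility open.

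**Definition.** Movement, pain, strength and function are in substance what the CM measures. Calling failure to improve on them an adverse event reports one result twice, once as efficacy and once as harm. Among 44 patients, a few genuine injuries could be lost in such a count.

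**Working it through.** The article gives no figure of its own on harms, so there is none to reproduce. The contact figures follow from the Intervention section.

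**1. Scheduled physiotherapist contact**
- PT: 12 weeks x 5 days = 60 sessions, if every programme day is attended in person.
- TR: 3 sessions x 30 minutes = 90 minutes in total.
- Ratio: 60 / 3 = 20.

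**2. Adding the evaluator visits at 4, 8 and 12 weeks, which both arms share**
- PT: 60 + 3 = 63. TR: 3 + 3 = 6. Ratio: 63 / 6 = 10.5.
- This is generous to the plan, since no harm question is described at those visits.

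**3. Sensitivity to the reading of PT**
The PT content includes home exercise, so 60 is the upper reading. Assume k in-person days per week, with k from 1 to 5.
- Physiotherapist contacts: 12k / 3 = 4k, so 4:1 at k = 1 and 20:1 at k = 5.
- With evaluator visits: (12k + 3) / 6, so 2.5:1 at k = 1 and 10.5:1 at k = 5.

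**4. TR exercise days without scheduled physiotherapist contact**
12 x 5 = 60 exercise days. If each videoconference falls on a separate exercise day, 60 - 3 = 57 days have none.

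**5. What unequal capture could do (illustration only)**
The article gives neither a harm rate nor a capture probability. Assume 22 patients per arm (the article's sample size), the same true harm rate of 20% in both arms, and 90% capture in PT. Expected recorded events = 22 x rate x capture.

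| Capture in TR | Recorded in PT | Recorded in TR | TR/PT ratio (true ratio 1) |
|---|---|---|---|
| 90% | 22 x 0.20 x 0.90 = 3.96 | 3.96 | 1.00 |
| 70% | 3.96 | 22 x 0.20 x 0.70 = 3.08 | 0.78 |
| 50% | 3.96 | 22 x 0.20 x 0.50 = 2.20 | 0.56 |
| 30% | 3.96 | 22 x 0.20 x 0.30 = 1.32 | 0.33 |

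The true rate cancels from the ratio, which is capture in TR divided by capture in PT. Over true rates of 10% to 30%, PT records 1.98 to 5.94 events and TR 0.66 to 5.94. The first row shows that with equal capture there is no bias.

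**6. Overlap of the adverse-event list with the primary outcome**
The Discussion lists non-improvement in movement, pain, strength and function. Primary outcome measures gives the CM domains as pain (15 points), daily activities (20), painless motion (40) and abduction strength (25). Three items match a CM domain directly, and function corresponds to daily activities.

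**The case against.** The strongest case against has five parts.

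- **A condensed article.** A harm form may stand in the full protocol, and nothing says that the 4-, 8- and 12-week visits exclude harm questions. This stands as a limit: the absence of a form is not the finding. The finding rests on the routes the article does state and on the contact it assigns to each arm.
- **No harms comparison is planned.** Objectives, outcomes and Statistical analysis cover CM, SST, satisfaction and cost. This stands. No planned test or estimate is biased; the exposure is to any statement on relative safety made when the results are reported.
- **Shared visits reveal lasting injury.** An injury that persists to a visit could lower the CM score in either arm under blinded assessment. This stands for lasting injury. Events that arise and resolve between visits remain exposed.
- **The recording sentence may cover TR only.** This cannot be settled from the text. If so, physiotherapist recording is stated for TR and not for PT. The arms would still not be recorded alike, but the direction of bias would be less certain.
- **The adverse-event text is a Discussion remark and not a formal endpoint, and injuries have their own sentence.** This is fair. It means injuries can be tabulated apart, so it would go too far to call every event count uninterpretable.

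A reader might infer that TR harms will certainly be under-recorded, and that counting non-improvement contributes to this. The document supports neither. Patients can report events themselves, and phone or email help exists, although the Discussion describes it for technical difficulties. Counting non-improvement adds events and so cannot cause under-recording.

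**Conclusion.** The point holds as a risk of differential ascertainment plus a separate fault of definition.

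- **Ascertainment:** scheduled physiotherapist contact is 3 sessions in TR against up to 60 in PT. This is 20:1 at most, and 10.5:1 on the same reading with the shared evaluator visits. It is a ratio of opportunities to notice harm, not of detection. The bias would probably favour TR, on the assumption that physiotherapist notes are kept in both arms or that more contact brings more recording. Its size cannot be derived from the document, and the ratios of 0.33 to 1.00 above rest wholly on assumed capture rates.
- **Definition:** listing lack of improvement as an adverse event counts the CM outcome again as harm and can obscure the overload injuries named alongside it.

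The primary CM analysis is not affected by either problem.

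**What to change.** 1. At the existing 4-, 8- and 12-week visits, give both arms the same short adverse-event checklist, for example new or worse pain, suspected strain or tendon inflammation, and unplanned health contacts. Have patients complete it themselves and keep it from the evaluator, so that blinding is protected.
2. Name this checklist as the source for any between-arm statement on harms. Physiotherapist notes and spontaneous reports can be listed as supplementary, and the text should say which arm or arms the physiotherapist's recording covers.
3. Tabulate injury events separately. Take lack of improvement out of the adverse-event list and report it only under CM and SST.

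Cost: a one-page form at three visits that already take place, a few minutes per visit, and slightly more events recorded.
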